### Randomization

After evaluation of the eligibility criteria, the subjects will be randomly distributed into the three intervention groups. Randomization numbers will be generated using envelopes, which will contain a card stipulating to which group the subject will be allocated. The envelopes will be sealed and opaque in texture, in order to ensure confidentiality. Participants will be allocated, enrolled, and assigned to the study by two assistants who will not participate in the intervention stage. Participants will be contacted by telephone.

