### Subjects

Adult patients with Down syndrome (DS), aged between 18 and 40 years, will be recruited from institutions for people with disabilities. The survey will be conducted at the Center for Bioscience Applied to Patients with Special Health Care Needs (CEBAPE), Institute of Science and Technology—UNESP/SJC, Brazil. The study will include adult patients with DS, from both genders, presenting subjective sleep disorder symptoms, snoring, and/or apnea/hypoapnea index (AHI) > 5.0/h, satisfactory dental health, and preserved cognitive function which allows them to understand and to respond to verbal commands necessary to perform this research project, and who agree to participate by free will including an Awareness Term signed by the patient or by the people responsible for the patient. The researchers will obtain informed consent from assistants, patients, and/or caregivers prior to the study. Cognitive analysis will be carried out under simple commands, such as “open your mouth”, “close your mouth”, “bite”, and “relax”. If patients are able to answer these simple commands, then they will be considered as part of the study. The exclusion criteria include body mass index > 30, use of psychiatric medication, inability to reach the university when needed, signs of psychiatric disease, and having been exposed to physiotherapy and/or orthodontic treatment at least 6 months prior to the beginning of this study.

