#### Phases of the surface electromyography examination

The sEMG, referring to the bilateral masseter (surface portion) and to the temporal (anterior portion) muscles in rest, MVC, MHI, and bite force, shall be carried out in two distinct phases: Phase 1, initial data acquisition, prior to proposed therapies (Groups 1–3); and phase 2, treated groups (Groups 1–3) after 2 months of neuromuscular electrical stimulation, mastication apparatus with mastication instrument Hiperboloide®, and mandibular advancement oral appliance therapies. The obtained data will be compared among each group and among each person with themselves, to verify the effectiveness of the proposed therapies on the improvement of the masticatory muscle electrical activity, on the physiological sleep variables, and on salivary parameters in patients with DS.

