#### Protocol for polysomnography

All patients will undergo the PSG type II home sleep test (Embla Embletta MPR + PG ST + Proxy; Natus, CA, USA) in their own house. The PSG will be performed prior to and after 2 months of all proposed therapies. During the night, a sleep technician will visit each patient’s home for examination preparation. All recording sensors will be placed according to recommended PSG techniques, using a gel-covered transducer, tapes, or elastic straps. The following biological signals will be recorded simultaneously and continuously: six channels for the electroencephalogram (EEG) (F4–M1, C4–M1, O2–M1, F3–M2, C3–M2, O1–M2), two channels for the electrooculogram (EOG) (E1–M2, E2–M2), four channels for the surface electromyogram (muscles of the submentonian region, anterior tibialis muscle), one channel for the electrocardiogram (derivation V1 modified), two channels for airflow (oronasal thermistor, nasal pressure transducer), two channels for respiratory effort (chest and abdomen, via x-trace belts), one channel for snoring, and one channel for body position, via EMBLA sensors. Arterial oxygen saturation (SaO_2_) and heart rate will be recorded via an EMBLA oximeter. All sleep staging and EEG arousals, respiratory events, and leg movements will be visually scored according to the *American Academy of Sleep Medicine (AASM) Manual for the Scoring of Sleep and Associated Events*, version 2.2, which is the definitive reference for standardized sleep monitoring and scoring [37]. The patients will be instructed to remain as relaxed as possible and to sleep naturally, as if at home. All signals will be recorded continuously. In the morning, an experienced polysomnography technician will remove the PSG equipment from the patient. A sleep physician will read and interpret all PSG examinations.

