### Statistical analysis

Whenever applicable, the data will be presented as average ± standard deviation. The paired *t* test will be used in order to compare continuous variables with normal distribution, prior to and after polysomnography, as well as specific therapies. If the data show a non-normal distribution, then the Wilcoxon test will be used. The groups will be compared to one another using ANOVA or Mann–Whitney U test, according to the distribution. *P* ≤ 0.05 will be considered statistically significant. Missing data will be treated as worst-case scenario imputation. All analyses will be performed using SPSS 16.0.

All data will be stored on a notebook exclusively for this purpose, as well as on a hard disk for increased safety of data storage. Data will be allocated to a file with a number that corresponds to each participant and will be managed by the assistants, not available to the professionals who will carry out the interventions.

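### Envelopes are named as the source of the allocation, and the same two assistants enrol and assign, so selection bias is not excluded; the text also does not require baseline tests to precede allocation

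*Protocol article*

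**What the plan says.** The relevant text is in four places in the protocol article.

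- **Randomization, source of the sequence.** "Randomization numbers will be generated using envelopes, which will contain a card stipulating to which group the subject will be allocated". The only concealment measure stated is this: "The envelopes will be sealed and opaque in texture, in order to ensure confidentiality". No list, shuffle, block or envelope numbering is mentioned.
- **Randomization, people and trigger.** "Participants will be allocated, enrolled, and assigned to the study by two assistants who will not participate in the intervention stage". Allocation is tied to one preceding step: "After evaluation of the eligibility criteria, the subjects will be randomly distributed into the three intervention groups".
- **Subjects.** Entry criteria include satisfactory dental health and the ability to follow simple commands. They also include patients "presenting subjective sleep disorder symptoms, snoring, and/or apnea/hypoapnea index (AHI) > 5.0/h".
- **Timing of baseline.** Electromyography and bite force: "Phase 1, initial data acquisition, prior to proposed therapies (Groups 1–3"). Polysomnography: "The PSG will be performed prior to and after 2 months of all proposed therapies". Both are placed relative to therapy, not relative to opening the envelope.

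The Sample size section needs 10 subjects per group, adds five per group for dropout, and recruits 45. The Abstract also gives 10 per group as the minimum.

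**The concern.** Concealment protects one decision: whether the next candidate enters the trial. It works when the person making that decision cannot know or influence the next allocation. Here the article describes a method under which the envelopes produce the sequence, and it gives enrolment and assignment to the same pair. Opacity guards against reading a sealed card. It does not guard against remembering the cards already opened, or against taking a different envelope when no order is fixed.

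The three therapies make different demands on teeth and cooperation, and some entry criteria leave room for judgement. If patients with poorer dentition or cooperation were steered away from the appliance or the bite-exercise arm, the between-group comparison would be confounded. With 10 to 15 patients per arm, a few such patients would matter, and no analysis can reliably undo it.

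The second part concerns the baseline. Maximum voluntary contraction and bite force depend on effort, and the electromyographic signal is normalised to the highest readings from the contraction tasks (Analysis of surface electromyography data). If these tests were done after the arm was known, expectation could enter the before-after difference.

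**Working it through.** The plan gives no figure on this point, so there is nothing of its own to reproduce beyond the total: 3 × (10 + 5) = 45, which agrees with the article. The two calculations below are illustrations. They use 45 patients in three arms (Sample size) and assume equal allocation, which the article implies but does not state as a rule.

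**Reading A: one shuffled deck, 15 cards per arm.** Someone who has seen all earlier cards guesses the arm with the most cards left.

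- At each step the chance of a correct guess is max(a, b, c) / (a + b + c), where a, b and c are the cards remaining. Averaging over all shuffles gives 19.66 expected correct guesses in 45.
- 19.66 / 45 = 43.7%, against 15 / 45 = 33.3% by chance. That is about 4.7 extra correct guesses over the trial.
- The last k allocations are certain when all remaining cards belong to one arm. The expected number is 3 × Σ C(15, k) / C(45, k), summed over k = 1 to 15, which equals 3 × 15 / 31 = 1.45.

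**Reading B: each card an independent draw with probability 1/3.**

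- For a single arm, P(fewer than 10 of 45) = Σ C(45, i) (1/3)^i (2/3)^(45 − i), summed over i = 0 to 9, which is 3.70%.
- For any of the three arms the exact multinomial result is 11.1%. This is almost exactly 3 × 3.70%, because two arms rarely both fall below 10. Ten is the number the article deems necessary per group, and this is before any dropout.

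**What blocks would do.** With the same guessing rule, fixed blocks of known size give about 50% correct for blocks of 15, 53% for blocks of 9 and 61% for blocks of 3. Fixed small blocks are therefore easier to guess than the single deck. Blocking helps balance. It helps concealment only if the sizes vary and are unknown to the person enrolling.

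**Order of baseline tests.** Set side by side, the Randomization section requires only that eligibility has been evaluated, while the electromyography and polysomnography sections require only that therapy has not begun. Between these two points the visible text does not say where the envelope is opened. Because an apnea/hypopnea index above 5.0/h is one of the alternative entry criteria, polysomnography may come first for some patients. Nothing comparable places electromyography or bite force before allocation.

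**The case against.** The strongest reply has four parts.

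1. **Stated safeguards.** The envelopes are sealed and opaque. The two assistants take no part in delivering therapy, which weakens any motive to steer patients, and trial data "will be managed by the assistants, not available to the professionals who will carry out the interventions". This stands as mitigation. It separates assignment from treatment delivery, however, not from enrolment.

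2. **Who generates the sequence.** A reader might infer that the assistants generate it themselves. The text does not say so: it gives them allocation, enrolment and assignment, and is silent on who prepares the envelopes. It is also silent on who holds them and on who judges dental health or response to commands. To say that allocation is foreseeable, as a fact, goes beyond the document.

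3. **Order of baseline tests.** A reader might infer that baseline tests follow allocation with the arm known, especially from the label Groups 1–3 attached to the first phase. That label only identifies who is measured, and the second phase carries it too. The flowchart and the schedule figure would normally show the order, and neither is visible here. The Quality control section has the data from before and after therapy analysed by evaluators described as blind, although it does not clearly cover those who acquire the data. This objection stands in full: the order is open, not wrong.

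4. **Condensation.** An article may leave the algorithm, envelope numbering and custody to a fuller protocol. This is fair for those details taken alone. It does not answer the two things the article does state: the envelopes as the source of the numbers, and one pair of people for both enrolment and assignment.

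The percentages also rest on mutually exclusive readings, neither of them in the text, and the independent-draw reading fits poorly with a planned 15 per group.

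**Conclusion.** The concern holds in a limited form. The article names the envelopes as the source of the allocation and does not separate enrolment from assignment. Selection bias is therefore a risk that the described method does not exclude; there is no evidence that it would occur.

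Its size cannot be fixed from the document. If the stack is one shuffled deck of 15 per arm, foresight is modest: about 44% correct guesses against 33%, with on average 1.45 final allocations certain. If cards are independent draws, predictability is nil, but there is about an 11% chance that an arm falls below 10. These are alternatives and should not be added together.

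On the baseline tests the finding is narrower still. The visible text does not require electromyography and bite force to be complete before allocation, and the figures not shown may settle it. The point deserves correction because the remedy is cheap and the weakness cannot be repaired once patients have been allocated.

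**What to change.** Revise the Randomization section along these lines:

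- A computer-generated list in permuted blocks of randomly varying size, prepared by a team member who does not enrol patients and with the block sizes withheld from those who do.
- The list transferred to sequentially numbered, sealed, opaque envelopes.
- The two existing assistants given separate roles: one screens and enrols, the other holds and opens the envelopes.
- The next numbered envelope opened only after consent and all baseline tests (polysomnography, electromyography, bite force, saliva) are recorded, with the participant's number written on it before opening. If the flowchart or schedule already sets this order, repeat it in the text.

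The cost is one computer list and a fixed order of steps, with no extra staff or visits. The drawback is that therapy cannot start until the baseline tests are finished.

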### Sample size

Power analysis or Power test is the process used for determining the sample size for this study, using SPSS (version 22.0.0.0). This is based on a work entitled “Effects of Neuromuscular Electrical Stimulation on the Masticatory Muscles and Physiologic Sleep Variables in Adults with Cerebral Palsy: A Novel Therapeutic Approach” [15]. The intervention was considered to result in a minimum effect similar to the EMG activity of the masseter and temporalis muscles in disabled adults. Thus, the sample size obtained revealed that 90% reliability to identify a relevant outcome will be present at the bidirectional α level of 0.05 with 10 subjects deemed necessary in each group, to which five individuals will be added to compensate for possible dropouts. Due to the risk of withdrawal, 45 patients will be recruited.

### Study interventions

#### Clinical evaluation

Anamnesis will be performed in order to investigate the overall health, treatments, results, and prescription of drugs, medical and family history, parafunctional habits, and psychological aspects. Specific questionnaires will be applied to screen the risk of sleep breathing disorders, sleep quality, and excessive daytime somnolence, including the STOP-BANG, the Epworth Sleep Scale, and the Fletcher & Luckett questionnaires. These questionnaires also comprise the assessment of important sleep features and alterations such as time in bed, sleep time, snoring, gasping and drooling during sleep, the occurrence of nightmares, movement during sleep, and the appraisal of mood at awakening, among other questions. An oral examination will be carried out to address anthropometric data, dental and oropharyngeal status, including the evaluation of dental occlusion, tooth wear severity, number of lost teeth, the degree of tongue scalloping, and modified Mallampati and tonsil scores [33–35].

#### Electromyographical parameters

The eight-channel module (EMG System do Brasil) (Fig. 3) will be used to capture biological signals. This equipment consists of a conditioner with a bandpass filter with cutoff frequencies at 20–1000 Hz, an amplifier gain of 1000×, and a common mode rejection ratio > 120 dB. All data will be processed using specific software for acquisition and analysis (EMG System do Brasil), with a 16-bit analog to digital converter and a sampling frequency of anti-aliasing of 2 kHz for each channel. Active bipolar electrodes with a preamplification gain of 20× are included.

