#### Analysis of surface electromyography data

In order to obtain a frequency domain analysis, surface EMG signal processing will be carried out using specific routines conducted with the Matlab program, version 7.1 (The MathWorks Inc., Natick, MA, USA). In addition, the time domain analysis will be executed using the root mean square (RMS) of the EMG signal (expressed in μV) and will be normalized by the highest values of RMS obtained during the three MHI and MVC readings (μVmV/μV/100: % MVC). The data captured at rest (total of 15 s) will be used for both analyses during MHI and MVC (total of 3 s; the first and fifth seconds having been discarded).

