#### Protocols for surface electromyography, mandibular force, and mouth opening

The selected protocol for sEMG is based on previous work [13, 15, 36]. The sEMG records will be acquired under the following conditions: rest (three sequential readings of 10 s each); maximum voluntary contraction (MVC) with cotton balls placed between the upper and lower molars on each side (three readings of 5 s each, with a 2-min interval between the readings); and voluntary contraction with maximum habitual intercuspation (MHI) with no material placed between the teeth (three readings of 5 s each, with a 2-min interval between the readings). After a 3-min interval, a mandibular force transducer (EMG System do Brazil) (Fig. 5) will be used to record the maximum bite force. This consists of a mechanical device with sensors that record material deformations during the bite. These deformations are converted into kilograms-force or Newtons by means of EMG Lab V1.1 software (EMG System do Brazil). The maximal opening amplitude will be measured with a specific caliper (Fig. 6).

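### Resting EMG goes into the frequency analysis over a band reaching half the sampling rate; if resting signal-to-noise is low, a pure amplitude gain would also read as a fall in frequency

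*Protocol article*

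**What the plan says.** The section Electromyographical parameters describes a conditioner with "a bandpass filter with cutoff frequencies at 20–1000 Hz" and "a sampling frequency of anti-aliasing of 2 kHz for each channel". The only noise-related hardware figure is "a common mode rejection ratio > 120 dB". No baseline noise in µV and no filter order is stated.

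The section Analysis of surface electromyography data plans two analyses. One is spectral: "In order to obtain a frequency domain analysis, surface EMG signal processing will be carried out using specific routines". The other is in the time domain: "the time domain analysis will be executed using the root mean square (RMS) of the EMG signal", normalized to the highest value from the maximum habitual intercuspation (MHI) and maximum voluntary contraction (MVC) readings. It then says: "The data captured at rest (total of 15 s) will be used for both analyses during MHI and MVC". The sentence is garbled, but its natural reading is that resting data enter both the RMS and the spectral analysis. It uses 15 s of rest, while the recording protocol specifies "rest (three sequential readings of 10 s each", which is 30 s. Which 15 s are kept is not said.

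No frequency index (median or mean) is named, in that section or among the outcomes.

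**The concern.** An upper cutoff at half the sampling rate leaves no room for the filter to roll off. With the usual definition of a cutoff, 71% of amplitude still passes at 1000 Hz, and what passes above it folds back into the band. For a strong contraction this hardly matters. At rest the EMG is much smaller, and the noise admitted across 20–1000 Hz can form an appreciable part of the recorded spectrum.

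When that happens, a frequency index depends on how far the EMG stands above the noise as well as on the muscle. Raise the EMG amplitude, leave its spectral shape alone, and the noise share falls; the index falls with it.

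This trial invites such a reading. Aims and hypotheses expects NMES and the mastication apparatus to change electrical activity at rest as well as in contraction. The Background links NMES to changes in muscle fibre composition, so a fall in resting frequency could be taken as a second, physiological effect. All three arms are active and the main comparisons are before against after, so no untreated arm would expose an artefact that follows resting amplitude. Normalizing RMS does nothing for a frequency index.

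**Working it through.** The plan states no figure that can be reproduced here, so the check asks what follows from its stated settings.

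**From the protocol:** band-pass 20–1000 Hz; sampling 2 kHz per channel; rest data in both analyses.

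**Assumed, because the protocol does not say:** EMG/noise RMS ratio r from 0.5 to 5; flat (white) noise; EMG power spectrum proportional to f² / [(f² + 60²)(f² + 120²)²], whose own median is about 97 Hz; Butterworth low-pass at 1000 Hz, order 4.

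**Step 1, guard band.** Half the sampling rate = 2000/2 = 1000 Hz, equal to the cutoff. The guard band is zero.

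**Step 2, folding.** Noise power folded back from above 1000 Hz, relative to in-band noise power, is 29%, 11% and 5% for filter orders 2, 4 and 8. Folded EMG is at most 0.2% of EMG power in every case tried.

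**Step 3, noise share at rest.** Share = 1/(r² + 1). Ratio 0.5: 1/1.25 = 80%. Ratio 1: 1/2 = 50%. Ratio 3: 1/10 = 10%. Ratio 5: 1/26 = 4%.

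**Step 4, a pure 50% rise in EMG amplitude.** EMG power is multiplied by 1.5² = 2.25; spectral shape and noise stay fixed. Median frequency is read from EMG plus noise over 20–1000 Hz. The apparent RMS change is √[(2.25r² + 1)/(r² + 1)] − 1.

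| r | Median frequency, before to after | RMS arithmetic | RMS reads as |
|---|---|---|---|
| 0.5 | about 398 to 274 Hz | √(1.5625/1.25) = 1.118 | +12% |
| 1 | about 184 to 129 Hz | √(3.25/2) = 1.275 | +27% |
| 3 | about 104 to 100 Hz | √(21.25/10) = 1.458 | +46% |
| 5 | shift of about 1 Hz | √(57.25/26) = 1.484 | +48% |

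The RMS column takes the reference contraction as unchanged. Mean frequency is more sensitive than the median: shifts of about −62, −74, −21 and −8 Hz at these four ratios (flat noise, no folding). At MVC, where EMG far exceeds noise, there is no shift.

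**Step 5, which part does the harm?** With flat noise and no folding, the medians are 393 to 270 Hz at ratio 0.5, 183 to 129 Hz at ratio 1, and 104 to 100 Hz at ratio 3. That is almost the same, so the effect comes from broadband noise in a wide band.

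**Step 6, other spectral shapes.** With EMG medians of about 52 and 144 Hz, the false median shift at ratio 1 is −47 and −53 Hz, against −54 Hz for the middle shape (no folding).

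**Step 7, a 20–500 Hz band (no folding).** The false median shift falls from −123 to −40 Hz at ratio 0.5, from −54 to −14 Hz at ratio 1, and from −4 to −2 Hz at ratio 3. The noise shares s become 0.66, 0.33 and 0.05. By √[2.25(1 − s) + s] − 1, the +50% then reads as √1.425 = 1.194 (+19%), √1.8375 = 1.356 (+36%) and √2.1875 = 1.479 (+48%). The effect is smaller but not gone.

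**The case against.** Four stronger readings are tempting, and the document supports none of them.

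- **That the resting spectrum is largely noise.** This needs an EMG/noise ratio below 1, and the protocol gives neither level. It does describe noise control: active preamplified electrodes, skin cleaning and a high common mode rejection ratio. The last acts on interference common to both electrodes, not on broadband electrode or amplifier noise, but together these measures mean low signal-to-noise cannot be taken for granted.
- **That anti-aliasing fails.** Without the filter order or converter design this cannot be shown. A cutoff at half the sampling rate is not a contradiction, and EMG itself is hardly folded.
- **That the sampling rate causes the false shift.** Steps 5 and 7 show otherwise: the shift is nearly unchanged without folding and persists, smaller, in a narrower band.
- **That a trial conclusion is affected.** No frequency index appears among the outcomes or in Statistical analysis. The effect on RMS is an understatement of gain, which is conservative.

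It is also fair that an article need not list its Matlab routines, which may already filter more narrowly, and that the sentence on resting data is ambiguous. These points limit the finding without removing it. The band, the sampling rate and the use of resting data in both analyses are choices the article states, and a plain reading combines them.

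**Conclusion.** The point holds as a conditional one. Followed as written, the plan can produce a resting frequency result that is confounded with the amplitude change the therapies aim to achieve. Under the assumptions above, the false fall in median frequency for a true 50% gain is about 124 Hz at an EMG/noise ratio of 0.5, about 55 Hz at ratio 1, about 4 Hz at ratio 3, and negligible from ratio 5 upward. Resting RMS gains are understated over the same range, severely at the low end and little at ratio 3. The size rests on the signal-to-noise ratio, which the protocol does not give; the direction does not depend on the three EMG shapes tried. Spectral results from MVC are not in doubt. This is an inexpensive improvement, not a demonstrated error in a trial result.

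**What to change.** In Analysis of surface electromyography data:

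1. State one digital band-pass with an upper limit well below 1000 Hz (20–500 Hz, for example), applied identically at both visits before the RMS and spectral estimates.
2. Restrict the frequency-domain analysis to the MVC and MHI epochs.
3. Report RMS only for rest.
4. Reword the sentence on resting data so that it says which analysis uses it, and which 15 s of the 30 s recorded are kept.

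The cost is a few lines of code on data recorded in any case. The loss is a resting frequency result, which could not be interpreted unless adequate resting signal-to-noise were shown. The narrower band reduces the noise effect on resting RMS but does not remove it, so resting gains should still be read as possibly understated.
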